### Statistical analysis

The primary outcome is the IBD-DI ordinal measure at the end of the treatment period (1–2 years after transfer). We will compare groups using the Wilcoxon-Mann–Whitney test, and statistical significance set at P < 0.05.

Secondary outcome measures will be analyzed at study completion and interim time points by comparing participants in the intervention and control arms using Wilcoxon-Mann–Whitney test. In addition, repeated measures analysis will determine changes over time for the primary and secondary outcome measures at three timepoints (baseline, time of transfer, end of study).

Assessment of health services outcomes will be conducted by linking clinical to health administrative data. Likelihood of emergency department use and hospitalization after transfer will be compared using multivariable logistic regression analysis. Number of ED and outpatient visits will be determined using either Poisson regression or negative binomial regression. All models will include confounders reported in Canadian health services studies of IBD patients: age at diagnosis, age at transfer, sex, rural/urban household, and socioeconomic status.

Assessment of implementation outcomes will be determined using mixed methods (quantitative and qualitative) assessment, as described above.

Sample size calculation: The IBD-DI ranges in score from 0–100. The categories of disability are 0–20 (no disability), 20–35 (mild disability), 35–50 (moderate disability), and 50–100 (severe disability). In the original validation study of the IBD-DI, the mean score of patients was 35.3 ± 20.5. We would consider the goal of this transition program to allow AYAs to achieve a mean level of < 20 (no disability), presenting a 16-point decrease from the mean baseline, or a Cohen effect size (*d*) of 0.78.

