Assuming alpha-probability of 0.05, 46 patients would be required to achieve a power of 80% (23 in each group), and 62 patients would be required to achieve a power of 90% (31 in each group) (calculated using G*Power version 3.1.9.7). Assuming a drop-out rate of 25% in each group over the course of the study, we will aim to enroll 90 participants (45 in each group). This calculation is likely an underestimation of the study’s power. Two simulation studies have demonstrated that stratified randomization increases study power in trials with sample sizes < 100 [48, 49]. There is no established method for sample size calculation that accounts for stratified randomization [50]. We will limit enrollment to 40 participants from SickKids, and 25 from other sites in order to ensure distributed enrollment across sites and reduce the risk of health system bias.

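### The sample sizes given for 80% and 90% power match a one-tailed calculation, yet no one-sided test is declared; read two-sided, they give about 71% and 84%

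*Protocol article*

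**What the plan says.** All of the relevant text is in the Statistical analysis section of the protocol article, which includes the sample size calculation.

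- **Primary test.** For the IBD Disability Index at the end of treatment: "We will compare groups using the Wilcoxon-Mann–Whitney test, and statistical significance set at P < 0.05". No direction or number of tails is given.
- **Effect size.** In the validation study of the index, "the mean score of patients was 35.3 ± 20.5". The planned difference is 16 points, expressed as a Cohen d of 0.78.
- **Sample size.** "Assuming alpha-probability of 0.05, 46 patients would be required to achieve a power of 80% (23 in each group"; the same sentence gives 62 patients (31 per group) for 90% and names G*Power 3.1.9.7. The number of tails is again not given.
- **Enrolment.** Allowing for 25% loss in each group, "we will aim to enroll 90 participants (45 in each group".
- **Comment on power.** "This calculation is likely an underestimation of the study’s power". The reason offered is that stratified randomization raises power in trials of fewer than 100 participants, with two simulation studies cited.

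**The concern.** A two-group comparison judged at P < 0.05, with nothing said about direction, is ordinarily taken as two-sided. The alpha, effect size, test, sample sizes and power are all stated in this section, so they can be checked against each other. On the two-sided reading they do not agree: 46 and 62 are about 20% below what that test needs (46/58 = 0.79; 62/76 = 0.82).

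Either reading leaves something to correct. If the test is two-sided, the stated pairings of sample size and power are wrong. If it is one-sided, the pairings are right, but the primary comparison would run at a 5% one-sided error rate that the article does not disclose. A two-sided P of up to 0.10 in the favourable direction would then count as significant.

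**Working it through.** **Inputs, all from the protocol article.** d = 16/20.5 = 0.78; alpha 0.05; 1:1 allocation (randomization section); Wilcoxon-Mann-Whitney test; 25% loss; 90 enrolled.

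**Method.** Noncentral-t power for the Wilcoxon-Mann-Whitney test with normally distributed scores. Each group size n is multiplied by the asymptotic relative efficiency, 3/π = 0.955. With m₁ = 0.955·n₁ and m₂ = 0.955·n₂:

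- degrees of freedom = m₁ + m₂ − 2
- noncentrality = d·√[m₁m₂/(m₁ + m₂)]
- critical value = t quantile at 1 − 0.05 (one-sided) or 1 − 0.025 (two-sided)

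**Step 1: reproduce the protocol's figures.** One-sided at 0.05:

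| n per group | df | noncentrality | critical t | power |
|---|---|---|---|---|
| 22 | 40.0 | 2.528 | 1.684 | 0.7996 |
| 23 | 41.9 | 2.585 | 1.682 | 0.815 |
| 30 | 55.3 | 2.952 | 1.673 | 0.898 |
| 31 | 57.2 | 3.001 | 1.672 | 0.907 |

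The smallest sizes reaching 80% and 90% are 23 and 31 per group, which are 46 and 62 in total. Both match exactly.

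**Step 2: the same inputs, two-sided at 0.05.**

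| n per group | df | noncentrality | critical t | power |
|---|---|---|---|---|
| 23 | 41.9 | 2.585 | 2.018 | 0.714 |
| 28 | 51.5 | 2.852 | 2.007 | 0.799 |
| 29 | 53.4 | 2.902 | 2.005 | 0.813 |
| 31 | 57.2 | 3.001 | 2.002 | 0.839 |
| 37 | 68.7 | 3.278 | 1.995 | 0.898 |
| 38 | 70.6 | 3.322 | 1.994 | 0.906 |

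Two-sided, 80% power needs 29 per group (58) and 90% needs 38 per group (76). The protocol's 46 and 62 give 71% and 84%. A simulation with normal data (20,000 runs) gave 70.8% at 23 per group and 83.8% at 31.

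**Step 3: could another two-sided method give 46 and 62?** Totals for 80% and 90% power, two-sided:

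| Method | 80% | 90% |
|---|---|---|
| Normal approximation | 52 | 70 |
| t-test | 54 | 72 |
| Wilcoxon-Mann-Whitney, normal scores | 58 | 76 |
| Wilcoxon-Mann-Whitney, minimum efficiency (0.864) | 64 | 84 |
| Wilcoxon-Mann-Whitney, logistic scores | 50 | 66 |
| Wilcoxon-Mann-Whitney, Laplace scores | 36 | 48 |

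None reproduces either figure.

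**Step 4: enrolment.**

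- The protocol's 90% figure inflated for loss: 62/0.75 = 82.7, so 83. Enrolling 90 covers this, but only under the one-sided calculation.
- Two-sided 80%: 58/0.75 = 77.3, so 78 enrolled.
- Two-sided 90%: 76/0.75 = 101.3, so 102 enrolled.
- The plan as it stands: 90 × 0.75 = 67.5, about 67 completers. With 33 and 34 per group, noncentrality is 3.119, critical t is 1.999 and two-sided power is 0.867.

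**The case against.** The article never says that the test is two-sided. That reading rests on convention. The stated aim is directional (a lower mean disability score), and the full protocol or analysis plan, not shown here, may state the number of tails. If the test is one-sided, 46 and 62 are correct and the only defect is non-disclosure. This stands, and is why the point is put conditionally. It does not remove the point, because the published section fixes the other design quantities and leaves out the one on which they depend.

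Several stronger readings are tempting but not supported:

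- **That the trial is underpowered.** The 71% and 84% belong to 46 and 62 completers. The plan expects about 67, for which two-sided power is about 87%. Two-sided power stays at 80% or more until loss exceeds about 35% (1 − 58/90 = 0.356). The article states no power for the trial as enrolled, so the 90% target is an inference from 62/0.75 = 83.
- **That the authors themselves foresee a two-sided question.** The Limitations section says controls may have better results through repeated measurement and monitoring. That describes controls improving and the contrast shrinking. It does not describe a hypothesis that the intervention is worse.
- **That the planned difference should be 15.3 points (35.3 to 20).** The goal is a mean below 20, and 35.3 − 16 = 19.3 meets it.
- **That the sentence on underestimated power is false and must go.** It rests on a separate argument about stratified randomization. The sidedness problem shows that the starting figures are too favourable; it does not refute that argument.

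**Conclusion.** The point holds in limited form. The two sample sizes match a one-tailed Wilcoxon-Mann-Whitney calculation exactly, and no one-sided test is declared. Read two-sided, the stated power is about 9 percentage points too high at 46 patients (80% against 71%) and about 6 too high at 62 (90% against 84%). For the trial as planned the shortfall is about 3 points against the implied 90% (87%), and the conventional 80% is met with room to spare.

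These figures assume d = 0.78, normally distributed scores, 25% loss and a two-sided test. The first and third are the protocol's own, the second is the setting that reproduces its sample sizes, and the fourth is convention. The finding concerns the wording and figures of the sample size paragraph. It gives no reason to change the endpoint, the test or the number enrolled.

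**What to change.** Revise the sample size paragraph as follows:

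1. State that the primary test is two-sided at 0.05.
2. Replace 46 and 62 with 58 and 76 completers for 80% and 90% power at d = 0.78.
3. State that 90 enrolled with 25% loss (about 67 completers) gives about 87% power. If 90% is to be kept as a target, about 102 would have to be enrolled.
4. If a one-sided 5% test is intended instead, keep 46 and 62, declare the one-sided test in both the analysis and sample size text, and justify it before data are seen.
5. Qualify the sentence on underestimated power so that it refers only to a possible, unquantified gain from stratified randomization.

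The cost is one paragraph of rewording and a slightly less favourable power statement. No extra patients are needed if about 87% is accepted. The Data Availability section says recruitment had not begun at submission, so at that stage the choice could be fixed without sight of any data.

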### Ethical considerations and consent to participate

This study has been approved by the Research Ethics Boards of SickKids (1000078476) and CHEO (21/143X), and is under review by Research Ethics Boards from the other participating centers. In Canada, there is no ‘age of majority’ for medical treatment or research consent. Adolescents can consent to treatments and research if they are deemed competent and informed. Informed consent will be obtained from the adolescents by research staff. The navigators will discuss the limits of participant confidentiality with participants and their families, emphasizing that the five domains of health will be discussed with the healthcare team to initiate appropriate interventions.

### Data management

Study data will be managed by a study-specific data coordinating center. The data management team will be led by [name] and members of the data coordinating center of CIDsCaNN.

## Discussion

The incidence of childhood-onset IBD is rising, resulting in more patients undergoing transition from pediatric to adult care. Caring for patients during the transition process has been identified as a major issue in the health care of AYAs with IBD [51], and a failed transition jeopardizes the health of this fragile population. This study is the first RCT to evaluate a systematic and structured intervention to improve transition of IBD patients whilst studying its’ implementation.

A recent systematic review identified transition interventions reported in the literature in patients with IBD and other pediatric-onset chronic disease [52]. No RCT has been conducted in transitioning IBD patients. However, interventions reported in observational studies include transition clinics which include a multi-disciplinary team with adult and pediatric providers, educational programs which include self-efficacy and other skills-building, and structured transition programs [25, 53, 54]. RCTs conducted in transitioning adolescents with other chronic diseases are also sparse [52]. There are two active RCTs being conducted in Canada to evaluate transition navigators in adolescents with chronic diseases in Alberta [55], and group education in adolescents with type 1 diabetes [56]. These interventions were integrated as part of our plans for a multimodal intervention.

We acknowledge the complexity of running a multimodal intervention that aims to build transition related skills across a variety of healthcare situations (pediatric vs. adult care, multidisciplinary care pediatric care teams vs. single adult healthcare providers, regional and healthcare system differences, etc.) This presents unique operational challenges relating to the fidelity of intervention implementation. Centralization of the transition navigators, skills-building and educational modules is a targeted approach to offsetting these dilemmas. These navigators will be tasked with documenting and adapting their interactions to suit individual and local needs while preparing for the training of future navigators assuming the program were to expand.

While pediatric care has traditionally operated with a more fulsome allied healthcare team, adult IBD healthcare providers have mostly worked as single providers in a variety of settings from outpatient private offices to tertiary care IBD centers. Because many adult providers work in a community setting, their interaction and level of engagement with the interventions of this trial is hard to predict. We anticipate that transition navigators may have more challenges interacting with the adult team and for this reason the intervention arm should have a degree of independence and the necessity of well trained and experienced navigators to the current and future success of the program.

### Strengths

The primary strength of this study is that it is a collaborative but directed intervention which has the potential to meet the transition needs of a diverse group of patients being treated in a diverse variety of settings. The study builds off knowledge and experience garnered in other transition populations and the core components have been designed with the input of a multidisciplinary multi-specialty group of experts with high interest and experience in this area. There is an effort to study impact with regards to clinical outcomes, health resource utilization and economic cost. Finally, this study integrates an implementation science approach to ensure the fidelity with which the intervention is applied and the adaptive process which must occur at each local level to ensure its success.

### Limitations

Replicability may be perceived as a limitation of this RCT, considering the complexity of the intervention and specific resources required to implement it. In addition, the pragmatic nature of this RCT will allow for revision and improvement of the interventions to best suit the needs of the participating AYAs, which means the interventions are not static in time. Finally, our intervention may be specific to the context of the Canadian healthcare system. We will endeavor to publish details on the development and evaluation process of each component of the intervention in separate scientific manuscripts prior to the end of the trial period to allow for adaptation of the intervention to other health systems. However, we anticipate that the specific details of each component of the intervention are less important than the overall approach to intervention with a navigator-supported bio-psychosocial and educational framework. If the intervention is deemed effective in this trial, a quality improvement evaluative framework will be developed upon implementation of the intervention in clinical practice in Canada.

We anticipate that study participants’ program adherence is a possible limitation. As part of the Hybrid Type 1 design, we will monitor adherence carefully with detailed documentation provided by the navigator, and through activity/completion reports of the eLearning platform. We will determine why portions of the intervention were not completed and adapt the intervention at the time of widescale implementation to encourage fidelity. As part of this process, we anticipate that one or more components of the intervention may not be feasible. As we are measuring both clinical and implementation outcomes, we will be prepared to identify whether the failure is an *intervention failure* and/or an *implementation failure*. This knowledge will inform next steps prior to scale up in other settings.

Given that the intervention is strategically implemented over three years to ensure that age and developmentally appropriate skills are being reinforced during the transition years spanning pediatric into adult care, the concern regarding patient attrition is present. Given the typically high degree of engagement, parental oversight and multi-disciplinary involvement in pediatric care, the attrition risk is likely highest during early adult care. The transition navigators will be aware of this concern and use more provider-initiated interactions to sustain adherence and engagement.

The issue of sustainability is a concern. Healthcare administrators and patients have been involved to understand implementation challenges. The cost and cost-effectiveness will be monitored through health resource utilization. Finally, international groups must adapt and evaluate the intervention in the setting of other healthcare systems.

Finally, it is possible that the control group will have better results because of repeated research measurements, ongoing monitoring, and increased awareness of transition as an important health issue. We have attempted to design the control protocol to mimic standard practice but realize that monitoring bias may occur. However, this would reduce the risk of Type 1 error and provide more argument for wide implementation if efficacy is demonstrated.

## Conclusion

This multi-component prospective transition intervention study for pediatric onset IBD builds on the existing literature of observational research to improve patient outcomes, as well as RCTs in other pediatric chronic diseases. It offers a unique focus on implementation science and a credible opportunity for national and international dissemination of positive findings. When this RCT is complete, it will represent the highest-level evidence for a transition intervention for IBD patients.

## Data Availability

Not applicable. Patient recruitment and data collection was not yet initiated at time of submission of this manuscript.

## Abbreviations

AYA: Adolescent and young adult;
CHEO: Children’s Hospital of Eastern Ontario (Ottawa)
CBT: Cognitive behavioral therapy
CIDsCaNN: Canadian Children IBD Network
CRF: Case reporting form
IBD: Inflammatory bowel disease
IBD-DI: IBD Disability Index
IBD-SES-A: IBD Self Efficacy Scale for Adolescents
IM: Instant messenger
PACE: Promoting Access and Care through Centres of Excellence
RCT: Randomized controlled trial
SickKids: The Hospital for Sick Children (Toronto)
TRAQ: Transition Readiness Assessment Questionnaire
